**Methods/Design:**

Thirty-seven South German preschools were identified for this study and agreed to participate. Using a two-armed, controlled cluster-randomized trial design we test a participatory intervention with parents as the primary target group and potential agents of behavioural change. Specifically, the intervention is designed to engage parents in the development, refinement and selection of project ideas to promote PA and in incorporating these ideas into daily routines within the preschool community, consisting of children, teachers and parents. Our study is embedded within an existing state-sponsored programme providing structured gym lessons to preschool children. Thus, child-based PA outcomes from the study arm with the parent-focused intervention and the state-sponsored programme are compared with those from the study arm with the state-sponsored programme alone. The evaluation entails baseline measurements of study outcomes as well as follow-up measurements at 6 and 12 months. Accelerometry measures PA intensity over a period of six days, with the mean over six days used as the primary outcome measure. Secondary outcomes include childrens' BMI, a sum of averaged skin fold thickness measurements across multiple sites, and PA behaviour. Longitudinal multilevel models are used to assess within-subject change and between-group differences in study outcomes, adjusted for covariates at the preschool and individual levels. Teacher qualitative interviews monitor the intervention implementation process.

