#### Parent Questionnaire

A review of previous work assessing health-related behaviours of preschool children by parental proxies revealed few instruments with established psychometric properties. Whenever possible, we use items from existing surveys; in other cases, it was necessary to adapt items to clarify selected features and those specifically related to the intervention. The resulting survey, described below, focuses primarily on children's health behaviours and is completed by one or both of the child's parents. The survey was administered at baseline, six and 12 months and will enable a complementary assessment of intervention effectiveness.

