##### Secondary outcomes

• BMI

• Skin fold sum and central body fat (waist-to-height ratio)

• Physical activity (PA) behaviour via parent questionnaire [47]

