### Research Questions

We aim to show that the supplementation of state-sponsored gym lessons with a parent-focused participatory intervention:

1) leads to significantly increased physical activity intensity in preschool-aged children at 6 months compared with baseline, as measured by accelerometry

2) leads to significant decreases at 6 months compared with baseline in childrens' mean BMI, sum of skin folds and waist-to-height ratio

3) leads to significant improvement in childrens' PA behaviour at 6 months as assessed by questionnaire

4) leads to a significant increase from baseline in childrens' mean 1-minute heart rate recovery after submaximal exercise at 6 months

5) has sustained effects on primary and secondary outcomes stated above (i.e., no significant difference between 6 and 12 months measurements)

Research questions to be addressed using *qualitative techniques *include:

1) How well is the participatory intervention accepted and adopted by parents and teachers?

2) To what extent do participants feel the parent-focused participatory intervention is tailored to the local needs?

3) Do participants feel that the participatory intervention is feasible in the German preschool setting within the framework of an existing state-sponsored programme?

4) What are the barriers and facilitating factors that appear to impede or promote successful intervention implementation and outcomes?

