### Assessment of intervention effectiveness

The intervention effectiveness is assessed by an intention-to-treat analysis.

Descriptive statistical analysis will be performed on all outcome measures. If needed, data will be transformed to better meet the assumptions of standard inferential statistical tests. We will use multilevel models to account for the structure of our data and for missing data on any of the measurements. In the multilevel model, repeated measurement of outcomes for each child will be considered the first "level"; these data are nested within preschools, which represent the second level. Differences between intervention and control group in primary and secondary outcomes will be analyzed in terms of fixed effects in the multilevel regression model, with age, sex, SES, immigration status and baseline BMI/accelerometer counts included as covariates on the individual level. In secondary analyses, the effect moderation by the preschool context as rated by qualitative data, as well as the level of implementation and adoption of the intervention will be analyzed.

Previous work documents a higher prevalence of overweight [63] and lower levels of physical activity [64] among immigrants. Because of the potential public health implications, we will conduct subgroup analyses at the child level comparing outcomes for normal-weight versus overweight children and for immigrant versus non-immigrant children. Subgroup analyses at the preschool level will be performed for rural versus non-rural locations and intervention timing (autumn versus spring) to assess the presence of potential effect modifiers.

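### The effectiveness model names only baseline BMI and accelerometer counts as baseline covariates, so if baseline enters as a covariate, skin fold sum, waist-to-height ratio and questionnaire PA behaviour are not adjusted for their own collected baselines

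*Protocol article*

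**What the plan says.** Under Assessment of intervention effectiveness, the protocol article states: "Differences between intervention and control group in primary and secondary outcomes will be analyzed in terms of fixed effects in the multilevel regression model", and the sentence goes on "with age, sex, SES, immigration status and baseline BMI/accelerometer counts included as covariates on the individual level". This is the only covariate list given, and its only baseline measurements are BMI and accelerometer counts.

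The section Secondary outcomes lists BMI, skin fold sum, waist-to-height ratio and PA behaviour by parent questionnaire. Research question 2 is that the intervention "leads to significant decreases at 6 months compared with baseline in childrens' mean BMI, sum of skin folds and waist-to-height ratio". Research question 3 is that it "leads to significant improvement in childrens' PA behaviour at 6 months as assessed by questionnaire", with no mention of baseline.

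Baselines exist for all of these. Evaluation Design places outcome measurements before the intervention and at 6 and 12 months. For the questionnaire, "The survey was administered at baseline, six and 12 months".

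Two statements describe the structure of the model. The abstract says "Longitudinal multilevel models are used to assess within-subject change and between-group differences in study outcomes". The effectiveness section says "repeated measurement of outcomes for each child will be considered the first" level, with preschools as the second. Neither says whether the baseline visit is one of the repeated measurements.

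**The concern.** The list gives BMI and accelerometer counts their own baselines. It gives the other three secondary outcomes the baseline of a different variable. In a covariate-adjusted analysis, an outcome's own baseline is usually its strongest predictor, and here it has been measured and then left out of the list.

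With 37 preschools, randomised in strata of preschool SES and location only, chance differences between arms in baseline skin folds, waist-to-height ratio or PA behaviour are plausible. Baseline BMI would remove part of such a difference for the two body-fat measures. For questionnaire PA behaviour, baseline BMI or counts may remove little. What is at stake is needlessly wide intervals, and residual chance imbalance, in two of the three measures in research question 2 and in research question 3.

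**Working it through.** **The plan's own figures.** The article gives no precision figure for secondary outcomes, only a sample size for the primary one. With a difference of 19.05, an SD of 38.1, two-sided alpha 0.05 and power 0.9, the unrounded number per arm is 2 × (1.960 + 1.282)² / 0.5² = 84.06. With 504/24 = 21 children per preschool and ICC 0.1, the design effect is 1 + 20 × 0.1 = 3.0. The total is 2 × 84.06 × 3.0 = 504.4 (stated: 504), and 504/0.9 = 560 (stated: 560). These reproduce, and this point does not affect them.

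**Inputs for the precision check.**
- From the article: 20 control and 17 intervention preschools, 741 children, 10% loss, ICC 0.1. Children per preschool: 741 × 0.9 / 37 = 18.
- Assumed: r, the correlation of an outcome's own baseline with its follow-up; c, the correlation of baseline BMI with that own baseline. Baseline BMI is taken to correlate c × r with follow-up, and correlations are equal at child and preschool level. Age, sex, SES and immigration status are left out.

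**Reading A: baseline as covariate, follow-up values as responses.** Standard errors (SE) are in outcome SDs.
- No baseline: √[(0.1 + 0.9/18) × (1/20 + 1/17)] = √(0.15 × 0.1088) = 0.128.
- Own baseline: 0.128 × √(1 − r²).
- Baseline BMI: 0.128 × √(1 − (c × r)²).

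| r | c | SE, baseline BMI | SE, own baseline | Reduction |
|---|---|---|---|---|
| 0.5 | 0.8 | 0.117 | 0.111 | 6% |
| 0.8 | 0.6 | 0.112 | 0.077 | 32% |
| 0.9 | 0.3 | 0.123 | 0.056 | 55% |

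Simulating the same layout (1,500 trials per setting) at r = 0.8, c = 0.6 gives 0.130 with no baseline, 0.112 with baseline BMI, 0.079 with own baseline, and 0.079 with both. The reduction is 1 − 0.079/0.112 = 30%, so the variance is about halved. Over r from 0.5 to 0.9 and c from 0.3 to 0.8, the simulated reduction runs from 3% to 56%.

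If the listed baseline predicts nothing, as it nearly might for PA behaviour, the SE is 1/√(1 − r²) times that with own baseline: 1.15 at r = 0.5 and 1.67 at r = 0.8.

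**Chance imbalance at r = 0.8, c = 0.6.** A one-SD chance difference in the baseline means is 0.128. Unadjusted, it carries 0.8 × 0.128 = 0.102 SD into the follow-up difference. After baseline BMI adjustment, 0.8 × 0.128 × √(1 − 0.6²) = 0.082 SD remains.

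**Reading B: baseline as a level-1 response, arm-by-time contrast.** The change contrast has relative variance 2(1 − r), against 1 − r² with own-baseline adjustment. The SE ratio √[2(1 − r)/(1 − r²)] is 1.085, 1.054 and 1.026 at r = 0.7, 0.8 and 0.9, and 1.155 at r = 0.5. In a three-visit model on the planned 24 preschools of 21 (assumed preschool autocorrelation 0.8), the follow-up-only SE is 1.37 to 1.73 times that of the change contrast for r from 0.6 to 0.9. Most of the gain is then already captured.

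Reading B needs within-child correlation in the model, and the section names only two levels, visits and preschools. Taken literally, with residual variance 0.9 at each visit, the model-based SE of the change contrast is √(2 × 0.9/18 × 0.1088) = 0.104, against 0.077 for own-baseline adjustment at r = 0.8.

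**The case against.** The strongest reply is that the model is longitudinal. The abstract speaks of within-subject change, outcomes are measured at three visits, and repeated measurements form level 1. Each outcome's own baseline may therefore already be a response, as research question 2 seems to need. This stands as a possible reading. A reader might infer from the covariate list that the three outcomes are certainly analysed without their own baselines, and the text does not establish that. Against Reading B, naming baseline counts and BMI as covariates makes most sense if only follow-up values are responses. If baseline is a response, the same sentence puts baseline counts and BMI on both sides of their own models. Either way the sentence needs an edit.

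A second reply is that the slash is shorthand for the relevant baseline and that outcome-by-outcome covariates belong in an analysis plan. That may be the intention. But the article does not leave the matter open: it states a list for primary and secondary outcomes alike, and that list suits only two of them.

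A reader might also infer that research question 2 and the model target different quantities. With randomised arms and a linear model, the arm difference in change and the arm difference in follow-up given baseline covariates have the same expected value, so only precision and adjustment for chance imbalance differ.

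**Conclusion.** The point holds conditionally. If baseline enters as a covariate, the stated list gives skin fold sum, waist-to-height ratio and questionnaire PA behaviour the wrong baseline. Own-baseline adjustment would then reduce the SE by about 30% at r = 0.8 and c = 0.6, and by roughly 3% to 56% over the assumed range. All these correlations are assumptions, so an unqualified statement that much precision is lost is not supported. The planned demographic covariates are not in the calculation either.

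If baseline is a level-1 response with within-child correlation modelled, the SE is only about 3% to 9% above that of own-baseline adjustment for r from 0.7 to 0.9, though 15% above at r = 0.5.

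There is no bias. The primary outcome has its own baseline in the list, and the sample size is unaffected. This is an inexpensive correction to the analysis of secondary outcomes.

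**What to change.** State whether baseline is a covariate or a response, and make the covariate list agree. Either:

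1. **Baseline as covariate.** Replace the mention of baseline BMI and accelerometer counts with the baseline value of the outcome being analysed, and use only the 6- and 12-month values as responses. Skin fold sum, waist-to-height ratio and the questionnaire measure each then get their own baseline. BMI and accelerometry keep theirs.
2. **Baseline as response.** Keep all three visits at level 1, drop the outcome's own baseline from the covariates, and test the arm-by-time contrast with a child-level random effect.

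The two should not be combined, since that would put the same baseline value on both sides of the model. The cost is a line or two of analysis wording, because every baseline value is already collected. The choice should be fixed before outcomes are compared by arm.

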#### Sample size and power considerations

Previous published work provides little guidance on the extent to which PA-related outcomes in preschool children are inter-correlated. We therefore conservatively estimated the intraclass correlation coefficient (ICC) to be 0.1 ([65], personal communication concerning referenced trial). To detect a difference of 0.5 standard deviations (19.05 counts/15 seconds) between intervention and control group, assuming a standard deviation of 38.1 counts/15 seconds ([name], unpublished data from pilot studies in 4-5 year-old children) for accelerometry and an intraclass correlation of 0.1, with a power of 0.9 and alpha of 0.05 (two-sided), we estimated that a total of 504 children in 24 schools would be needed. We increased recruitment goals to 560 children (280 per arm) to account for a 10% loss to follow-up.

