### Recruitment and randomization

Of the 43 preschools applying for participation in the state-sponsored PA programme, we recruited 37 (86%) preschools and a total of 741 (78%) children (see figure 2). As previous research in children has shown differences in PA by physical setting [33] and in BMI by socioeconomic status [27], we stratified the randomization to balance preschool socioeconomic status (low, middle and high) and location (rural or non-rural) in both arms. Aggregate socioeconomic status (SES) of the preschool attendees was estimated by a tertile split based on information provided by the head teacher on the proportion of children from families with low SES or immigrant background. Because we hypothesized that a preschool's location (e.g., amount of green areas, big streets/highways and wooded areas) determined opportunities for PA, we developed a structured protocol to categorize preschools' setting as either rural or non-rural. Specifically, satellite views at a predefined altitude were examined independently by two research team members (Google Earth, accessed 6^th ^June 2008). Rural sites were defined as those that had forest, parks and green spaces within the cutout but no highways or industrial areas. All other preschools were categorized as located in a non-rural area. In each case, ratings were compared and differences were discussed until consensus was reached.

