**Figure 2 F2:**
[figure not shown]
**Evaluation design accounting for seasonal differences and using a waiting list control**. CONT = gym lessons (existing state-sponsored programme). INT = participatory parent-focused intervention plus simultaneous gym lessons. X1 and X2: randomization time points, X1 = autumn, X2 = spring. ---- children enrolled and measured, but no intervention/gym lessons.

Preschool assignment was blinded through the use of sequentially numbered, sealed envelopes. Preschools in the control arm (CONT) (n = 20; 371 children) receive the state-sponsored programme's gym lessons over six months as the sole intervention. Parents of children enrolled at preschools in the intervention arm (INT) (n = 17; 370 children) receive the participatory intervention, while their children also participate in the gym lessons. The participatory parent-focused intervention runs simultaneously with the gym lessons over the first six months, but continues for a total of at least nine months.

To account for seasonal differences in physical activity [34,35], the study was implemented at two time-points during the year: half of the preschools started the intervention in autumn 2008 with the other half starting in the spring 2009. To account for changes that occur as a consequence of physical maturation in children over time, the participatory intervention arm served as waiting list control during the first six months. Due to the participatory nature of the intervention, it was not possible to blind study participants or intervention providers. However, those involved in outcome assessment will be blinded to intervention assignment.

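### The planned power of 0.9 for 24 preschools matches a normal approximation; with 22 cluster degrees of freedom it is about 0.87, although the recruited trial exceeds 0.9

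*Protocol article*

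**What the plan says.** All the planning inputs are in the protocol article under Sample size and power considerations. The target is given as "To detect a difference of 0.5 standard deviations (19.05 counts/15 seconds) between intervention and control group", "assuming a standard deviation of 38.1 counts/15 seconds", with "an intraclass correlation of 0.1" and "with a power of 0.9 and alpha of 0.05 (two-sided" test). From these, "we estimated that a total of 504 children in 24 schools would be needed". The allowance for attrition follows: "We increased recruitment goals to 560 children (280 per arm) to account for a 10% loss to follow-up". No formula or degrees-of-freedom method is named.

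Recruitment and randomization reports that "we recruited 37 (86%) preschools and a total of 741 (78%) children". The text with Figure 2 splits these into 20 control preschools with 371 children and 17 intervention preschools with 370. Power is not restated for that design.

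Assessment of intervention effectiveness plans a multilevel model with preschool as a level. The arm difference is a fixed effect, and age, sex, SES, immigration status and baseline values are covariates.

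**The concern.** The preschool is the unit of allocation, so the precision of the arm comparison is limited by the number of preschools. With 24 of them, the between-preschool variance is estimated on about 22 degrees of freedom. The two-sided 5% critical value is then about 2.07 rather than 1.96. Multiplying an individual-level sample size by the design effect gives the right standard error, but it still treats the test statistic as normal. With this few clusters the result is a stated power that the stated design does not quite deliver.

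What is at stake is modest: the accuracy of the planning statement, and its use as a template, since the article's Discussion offers the design as a model for other preschool trials. A trial that copied 24 schools of 21 children on these assumptions, with no credit for covariates, would fall short of 0.9.

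**Working it through.** **Inputs (Sample size and power considerations).** Difference 19.05 counts, SD 38.1, so the standardized difference is 19.05/38.1 = 0.5. ICC 0.1. Two-sided alpha 0.05, power 0.9. 504 children in 24 schools is 504/24 = 21 per school; with 1:1 allocation, 12 schools and 252 children per arm.

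**Step 1: reproduce the stated figure.**
- Individual-level n per arm: 2 × (1.960 + 1.2816)² / 0.5² = 84.06.
- Design effect: 1 + (21 − 1) × 0.1 = 3.0.
- Per arm: 84.06 × 3.0 = 252.2. Total 504.4, and 504.4/21 = 24.02 schools.
- Normal-approximation power at 504: the SE in SD units is √(2 × 3/252) = 0.1543; 0.5/0.1543 = 3.240; Φ(3.240 − 1.960) = 0.8998.
- Attrition: 504/0.9 = 560.

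Every stated figure is recovered. A t test on 502 child-level degrees of freedom gives nearly the same power (0.899), so the match shows that cluster-level degrees of freedom were not used. It does not show which of these two tests the authors had in mind.

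**Step 2: the same design with cluster degrees of freedom.** Noncentral t, noncentrality 3.240, df = 24 − 2 = 22, equal school sizes, no covariate adjustment:

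| Schools of 21 | Children | Power, normal | Power, t (schools − 2 df) |
|---|---|---|---|
| 24 | 504 | 0.900 | 0.872 |
| 26 | 546 | 0.921 | 0.899 |
| 28 | 588 | 0.938 | 0.920 |

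The shortfall at 24 schools is 0.900 − 0.872 = 0.028. The difference detectable with power 0.9 in that design is 0.5235 SD × 38.1 = 19.95 counts, against the stated 19.05.

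**Step 3: the trial as recruited.** Control has 20 preschools and 371 children (mean 18.6); intervention has 17 preschools and 370 children (mean 21.8). After 10% loss the means are 16.7 and 19.6.
- Variance in SD² units: (1 + 15.7 × 0.1)/(20 × 16.7) + (1 + 18.6 × 0.1)/(17 × 19.6) = 0.00770 + 0.00859 = 0.0163; SE 0.1276.
- Noncentrality 0.5/0.1276 = 3.919, df = 37 − 2 = 35, power 0.968. Without loss it is 0.972.

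**Step 4: unequal preschool sizes.** The article does not report the spread of sizes, so the coefficient of variation (CV) is an assumption. The mean size m in the design effect is replaced by (1 + CV²)m.

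| Assumed CV | Planned 24 schools, 22 df | Recruited, 10% loss, 35 df | Recruited: difference for power 0.9 |
|---|---|---|---|
| 0 | 0.872 | 0.968 | 16.2 counts (0.425 SD) |
| 0.3 | 0.852 | 0.959 | 16.7 counts (0.438 SD) |
| 0.4 | 0.836 | 0.952 | 17.1 counts (0.448 SD) |

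**The case against.** The strongest reply is that nothing has been miscalculated. Individual sample size times design effect is a common planning formula, and every number follows from its inputs. That stands: the point concerns the choice of approximation.

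A second reply is that 0.87 is itself conditional. Neither the formula nor the degrees-of-freedom method is named, and the planned model adjusts for baseline accelerometer counts, which an unadjusted calculation ignores. With 22 df, a baseline correlation of about 0.30, if it reduces variance equally between and within preschools (factor 1 − 0.30² = 0.91), would restore 0.90; a correlation of 0.5 would give 0.947. An ICC of 0.087 in place of 0.1 would also give 0.90. The article reports no such correlation and describes its ICC as conservative, so the power of the planned adjusted analysis is unknown and may lie either side of 0.90. This limits 0.87 to the unadjusted comparison. It does not rescue the stated 0.9, because the sample size paragraph takes no credit for covariates.

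Two stronger readings are tempting. A reader might infer that the trial is underpowered; Step 3 shows that on the article's own assumptions it is not. A reader might also infer that the article offers 19.05 counts as the detectable difference of the trial it recruited, and so misstates its sensitivity. It does not: the paragraph is an a priori calculation about what would be needed, the recruited numbers are openly reported, and exceeding a target creates no duty to restate power. Nor are the unequal arm means of 21.8 and 18.6 evidence about the spread of sizes among the 24 planned schools.

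**Conclusion.** The point holds as a minor one. The stated power of 0.9 for 24 schools and 504 children is overstated by 2.8 percentage points: about 0.87 on the article's own SD, ICC and difference, given equal school sizes, 12 schools per arm, no covariate adjustment and 22 df. That the source was a normal approximation is an inference, though the match is close to exact. The practical consequence is small, because recruitment is complete and exceeded the plan by 37 − 24 = 13 preschools. The recruited design has about 0.97 power for 19.05 counts after 10% loss (0.95 to 0.96 at an assumed CV of 0.3 to 0.4), before any gain from baseline adjustment.

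**What to change.** Amend the sample size paragraph along these lines: the planned 24 preschools and 504 children gave a power of about 0.87 (unadjusted comparison, equal preschool sizes, t test on 22 df). As recruited (17 intervention and 20 control preschools, 741 children, 10% loss, ICC 0.1), the trial has about 0.95 to 0.97 power for 19.05 counts and 0.9 power for about 16 to 17 counts, before any gain from baseline adjustment. Name the formula and the degrees of freedom used, and say that the lower power and the upper detectable difference assume a CV of preschool size of up to 0.4; the actual CV can be put in, since the sizes are now known. Read a null result from the confidence interval for the arm difference, not from either power figure.

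The cost is two or three sentences. Recruitment and analysis do not change; the planned power looks slightly less favourable, and the recruited trial's sensitivity is put on record.
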